### Retention

Adherence and retention in E-LITE is fostered by: 1) selection/retention, training, and quality control of qualified staff; 2) the relationship between staff and participants, 3) willingness to accommodate participant schedules and needs, and 4) resourcefulness and persistence of the staff. A participant tracking database is used to assure that participants are contacted on a timely basis to obtain study data. The assessment staff will contact participants who miss a follow-up assessment to try re-engaging the patient in subsequent follow-ups. Ongoing monitoring of indices of participation in intervention activities helps interventionists identify participants who are having problems with adherence to the intervention protocol and thus qualify for recovery efforts. Such efforts can range from brief telephone discussion to an individualized counseling session with an interventionist in which the participant who makes a decision to discontinue intervention can review concerns regarding E-LITE, reasons for staying in E-LITE, and decisions about remaining a participant. Unless the participant declines, the interventionist will continue to contact the participant on a progressively less frequent schedule, starting monthly and decreasing to semi-annually to remind her/him of the opportunity to re-enter E-LITE and to maintain contact for possible recruitment for the final assessment at the end of E-LITE.

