#### Maintenance Phase

Both SM and CM interventions use secure online messaging as the primary mode of contact between participants and the dietitian during the maintenance phase. The contact time is likely to vary depending on individual needs in either intervention arm. The exercise physiologist is available to counsel the dietitian on issues related to physical activity but she will have no direct communication with participants in this phase. Participants are instructed to continue monitoring their weight, dietary intake, and physical activity at least twice each week.

SM condition. SM participants receive an email reminder every two weeks to continue self-monitoring. As in the Intensive Treatment phase, they are encouraged to submit comments and questions to the dietitian via secure messaging. The dietitian will respond to participant inquiries but will not initiate contact.

CM condition. In contrast, the dietitian provides active follow-up and individualized counseling to participants in the CM group via secure messaging on at least a monthly basis. Based on participant progress, the dietitian provides tailored feedback to reinforce progress, recommend problem solving and relapse prevention strategies, and encourage maintenance efforts. As the participant is successful or not in attaining his/her current goals, changes to the individual action plan are recommended, e.g., modifying goals, adding to them, or replacing them with new goals. The objective of any changes to the action plan is to keep the goals realistic yet challenging and to accommodate preferences and periodic fluctuations in motivation and schedule. Participants are encouraged to practice subject-initiated relapse prevention strategies, with feedback and support from the dietitian. Participants who fail to complete their self-monitoring diaries as scheduled are queried about their progress relative to their weight loss and behavioral change goals and any barriers they have encountered in attaining those goals. They are strongly encouraged to monitor and continue with the intervention. At the discretion of the dietitian, participants may be phoned or seen to address outstanding issues related to poor understanding of and/or adherence to the intervention protocol.

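### Interventionists re-contact drop-outs partly to secure the 15-month assessment, a channel usual care lacks; for SM in maintenance this also conflicts with the rule against dietitian-initiated contact

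*Protocol article*

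**What the plan says.** The Retention section of the protocol article describes two routes for keeping participants in the study.

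- **Assessment staff.** "The assessment staff will contact participants who miss a follow-up assessment to try re-engaging the patient in subsequent follow-ups". This is not tied to an arm, so it covers UC. A tracking database supports timely contact for data collection, again without reference to arm.
- **Interventionists.** The trigger is poor take-up of the intervention: "Ongoing monitoring of indices of participation in intervention activities helps interventionists identify participants who are having problems with adherence to the intervention protocol". On the form of recovery: "Such efforts can range from brief telephone discussion to an individualized counseling session with an interventionist". For those who decide to stop, and who do not refuse further contact, "the interventionist will continue to contact the participant on a progressively less frequent schedule", monthly at first and falling to twice a year. One aim is to remind them that they may re-enter. The other is "to maintain contact for possible recruitment for the final assessment at the end of E-LITE". No arm is named.

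The interventionists described are a dietitian and an exercise physiologist, and only for SM and CM. The Maintenance Phase section says of the dietitian in SM: "The dietitian will respond to participant inquiries but will not initiate contact". Of the exercise physiologist, in both active arms, it says: "she will have no direct communication with participants in this phase". In CM, by contrast, the dietitian follows participants up actively at least once a month.

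Data Analysis places the primary comparison, each intervention against UC, at 15 months by intention to treat. Sample Size allows up to 20% loss and gives one rate for all arms.

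**The concern.** The second route cannot operate in UC, which has no intervention activities to monitor and no interventionist to call. Yet one of its stated aims is attendance at the visit where the primary outcome is measured. Effort to obtain that outcome is thus arm-dependent by design, and it is directed at people who have stopped the intervention, whose weight course may well differ from that of others. If the extra effort changes who attends at month 15, the arms are compared on differently selected sets of participants.

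The second issue is one of consistency. Proactive dietitian contact is the main stated difference between CM and SM in maintenance, and the Aims say that the two interventions will be compared. A retention rule that has interventionists start contact with SM participants contradicts the SM description. It also leaves unclear what SM participants may receive.

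**Working it through.** **1. The plan's own figure.** Inputs from Sample Size and from Randomization and Blinding: N = 240, allocation 1:1:1, effect 0.5 SD, two-sided alpha 0.05, loss up to 20%.

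- Per arm: 240 / 3 = 80. Evaluable: 80 × (1 − 0.20) = 64.
- Power with 64 against 64: 0.801 (noncentral t), 0.807 (normal approximation). The stated 80% reproduces.

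**2. Does unequal retention harm power?** The rates are assumed, because the article gives only the single 20%. The t-test power for active/UC retention is:

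| Active / UC retention | n per arm | Power |
|---|---|---|
| 80% / 80% | 64 / 64 | 0.801 |
| 85% / 75% | 68 / 60 | 0.800 |
| 90% / 70% | 72 / 56 | 0.795 |
| 90% / 80% | 72 / 64 | 0.824 |

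Power barely moves, so the question is bias.

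**3. Bias in a completer contrast.** Let p be the proportion lost in an arm, and let non-attenders do worse than attenders by g (in SD of the outcome). The full-arm mean is the attenders' mean plus p × g, so the attenders' mean is too favourable by p × g. With the same g in both arms:

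shift in (UC − active) = −(p_UC − p_active) × g

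Take UC at the planned maximum of 20% and the active arm at an assumed 15%. This is 16 against 12 lost of 80.

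- g = 0.25: 0.05 × 0.25 = 0.0125 SD, and 0.0125 / 0.5 = 2.5% of the target effect.
- g = 1.0: 0.05 × 1.0 = 0.05 SD, and 0.05 / 0.5 = 10% of the target effect.

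If UC loses more, the benefit is understated. If the active arm loses more, the sign reverses. With equal loss and equal g, the shift is zero.

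**4. The SM texts side by side (months 3 to 15).**

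| Interventionist | Maintenance Phase, SM | Retention |
|---|---|---|
| Dietitian | answers inquiries, starts no contact | an interventionist phones, counsels or keeps contacting |
| Exercise physiologist | no direct contact with participants | same |

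No described interventionist may start contact with an SM participant in this phase, yet Retention has one do so and states no exception. Reading Retention as covering CM only would remove the conflict, but CM alone would then have the extra route to the final visit, relative to both UC and SM. In the first three months there is no conflict, because the Intensive Treatment Phase text for SM contains no such rule.

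**The case against.** The case on the other side has four parts.

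- **UC is followed up.** Assessment staff pursue anyone who misses a visit, in every arm. This stands: the asymmetry is an added channel in SM and CM, not an absence of effort in UC.
- **The extra channel may offset an extra loss.** Only SM and CM have an intervention to abandon, and so a reason for leaving that UC lacks. This also stands. A reader might infer that UC will lose more participants and that the effect is biased toward the null, perhaps by as much as 0.15 SD. The documents do not support that. The figure needs 30% loss in UC against 15% in an active arm and a full 1.0 SD gap (0.15 × 1.0), while the plan assumes at most 20%. The direction follows only from the rates chosen.
- **The analysis anticipates missing data.** The mixed model uses the 3- and 6-month measurements, and Data Analysis commits to sensitivity analyses with baseline carried forward, hot deck and multiple imputation. This stands in part. The model removes only what earlier visits explain, and the sensitivity analyses show how far the result depends on assumptions. Neither equalises the effort to obtain the outcome.
- **The SM rule concerns routine delivery.** On this view, Retention deals with people who have left, and its counseling session reviews their reasons for staying or going. That is a possible reading, but the article does not state it, and the recovery efforts also cover participants who merely adhere poorly. A reader might infer that SM will in practice come to resemble CM. The text does not show that: how many SM participants would be contacted is unknown, and SM against CM is not a primary comparison.

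**Conclusion.** The point holds in two limited parts.

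First, the plan gives the active arms an additional means of recruiting drop-outs to the primary-endpoint visit, which UC cannot receive. This is a risk of differential retention, not a demonstrated bias. The illustrated 0.0125 to 0.05 SD rests on an assumed 5-point difference in loss, an assumed common gap of 0.25 to 1.0 SD, and a completer analysis. With other rates, or gaps that differ by arm, the shift could vanish, grow or change sign. The stated power is sound and is not in question.

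Second, for SM in months 3 to 15, the Retention and Maintenance Phase sections contradict each other as written. This part rests on no numerical assumption.

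Both are worth correcting, because the remedy is cheap and the first bears on the primary comparisons.

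**What to change.** 1. Assign every contact meant to obtain the 15-month assessment to the blinded assessment staff, on one schedule for all three arms. Trigger it by the calendar or by a missed visit, never by discontinuation of the intervention: a referral for that reason would tell blinded staff that the participant is not in UC.
2. Limit interventionist contacts to intervention matters, including the offer to re-enter, and remove recruitment for the final assessment from their purpose.
3. Reconcile Retention with Maintenance Phase by stating which arms and phases the interventionist-initiated contacts cover. Which rule should apply to SM is for the investigators to decide.
4. Log any contact that an interventionist initiates with an SM participant, so that the SM against CM comparison can be read with that in view.

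The cost is a change of wording, a simple log and a modest shift of calls to assessment staff, who already re-contact participants. No new role is needed.

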### Sample Size Considerations and Statistical Analysis

#### Sample Size

Given the target sample size of 240, we expect approximately 80% power for detecting a net difference of 1/2 of a standard deviation (equivalent to a medium effect size of 0.5) in BMI at 15 months between the SM intervention and usual care (and similarly, between the CM intervention and usual care) at a 2-sided α level of 0.05, assuming up to a 20% rate of loss to follow-up. The effect size is estimated based on a number of successful lifestyle weight loss intervention studies [6,18-20]. The power estimate was calculated based on a t-test using simplified assumptions. Note that the t-test calculation is conservative because it does not account for variance reduction due to adjustment for baseline variables, nor for the better than chance comparability of the experimental groups. The primary comparisons of each intervention with usual care will be conducted using two-sided procedures at the overall significant level of 0.05. Multiplicity adjustments are not necessary because the primary interest is to estimate separate treatment effects for a limited number (i.e., n = 2) of key contrasts that pertain to different interventions [53]. Therefore, p-values of each comparison will be compared to type I error α = 0.05 for significance.

### Data Analysis

The primary hypothesis compares BMI between each intervention (SM and CM) and usual care at 15 months using an intent-to-treat analysis. Linear mixed modeling,

using SAS PROC MIXED [54] will test time and group interactions to asses whether within-subject change in BMI differs by condition. This basic analytical strategy also accounts for the nature of repeated measurements, the blocked design by cohorts, and the clustering of patients within physicians. The same analysis strategy is appropriate for evaluating secondary aims where the hypotheses are identical but with different outcome measures (e.g., glycemic control, other component risk factors of the metabolic syndrome, and psychosocial well-being). The longitudinal effects of the interventions will be assessed using the same model, except that the focus is comparisons within intervention groups at different time points. Analyses will also be conducted to examine whether there is a dose-response relationship between intervention adherence and outcome, where dose is defined in terms of number of group sessions attended, number of secure messages sent, number of self-monitoring logs, average daily intakes of calories and fat, and average number of minutes of physical activity per week.

For participants with missing outcomes at the primary (15-month) or secondary (3- and 6-month) assessment point, we will conduct and report on sensitivity analyses in which different imputation methods are used (e.g., the baseline-observation-carried-forward method, the "hot deck" procedure, and an appropriate multiple imputation method [55,56].

We will use the MacArthur approach, which modified the Baron & Kenny criteria, for defining moderators and mediators in clinical research studies [57]. Let T be the treatment, M be the potential moderator or mediator, and O be the outcome. Association between T, M, and O is examined using the following models:(1)

M is a moderator of the effect of T on O if M precedes T, γ_1 _= 0, and β_3 _≠ 0. M is a mediator of the effect of T on O if T precedes M, γ_1 _≠ 0, and either β_2 _≠ 0 or β_3 _≠ 0.

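### Secondary outcomes are tested through a time-by-group interaction with no stated common baseline mean or own-baseline adjustment, which can cost precision that is free to recover

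*Protocol article*

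**What the plan says.** The Data Analysis section of the protocol article specifies a linear mixed model that "will test time and group interactions to asses whether within-subject change in BMI differs by condition". For the other endpoints it adds: "The same analysis strategy is appropriate for evaluating secondary aims where the hypotheses are identical but with different outcome measures". The examples given there are glycemic control, the other metabolic syndrome components and psychosocial well-being.

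The same section says the strategy "accounts for the nature of repeated measurements, the blocked design by cohorts, and the clustering of patients within physicians". No baseline covariate is listed, and nothing is said about whether the arms share a baseline mean.

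Baseline adjustment appears only in the Sample Size section. The t-test power calculation for BMI is called conservative there because "it does not account for variance reduction due to adjustment for baseline variables". The variables are not named, and the remark is not extended to the secondary outcomes.

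Table 2 schedules CRP at baseline and 15 months only. Fasting glucose, lipids and A1c are scheduled at baseline, 6 and 15 months.

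**The concern.** A test of whether change differs by arm can be built in two ways that differ in precision. In the usual group, time and group-by-time model, each arm has its own baseline mean, and with complete data the 15-month interaction equals the difference in mean change from baseline. If the arms are instead held to a common baseline mean, which randomization justifies, the same interaction equals a comparison adjusted for the outcome's own baseline. The text does not choose between them, and the first is what the named procedure gives when no constraint is added.

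The choice matters little for an outcome that tracks closely within a person. It matters more for outcomes whose 15-month value is only loosely tied to baseline. There, real effects on glycemic control, cardiovascular risk factors or quality of life would be estimated with more noise than the collected data require.

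**Working it through.** **Inputs from the protocol article.** 240 participants are randomized 1:1:1, with up to 20% loss, a two-sided alpha of 0.05 and a difference of 0.5 SD. So 240/3 = 80 per arm at baseline and 80 × 0.8 = 64 at 15 months.

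**Assumptions.** The correlation rho between baseline and 15 months is not given, so a range is shown. The documents give no effect size for the secondary outcomes, so 0.5 SD is borrowed from BMI as an illustration. The SD is taken as equal at both visits, and loss as unrelated to outcome.

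**The plan's own figure.** A two-sample t-test with 64 per arm and 0.5 SD gives 80.1% power (80.7% by normal approximation). This reproduces the stated value of about 80% with no baseline adjustment.

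**Is baseline among the responses?** CRP has one follow-up visit, so a time-by-group interaction exists for it only if baseline is one of the time points. For glucose, lipids and A1c, a model of the follow-up visits alone would make the interaction ask whether the effect differs between 6 and 15 months. That is not the stated hypothesis.

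**Variance of the 15-month contrast**, in units of 2·SD²/64, for two visits (as for CRP), with all 80 baselines per arm used by the likelihood:

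- Free baseline mean per arm: the estimated change in an arm is the completers' 15-month mean, minus rho times the completers' baseline mean, minus (1 − rho) times the baseline mean of all 80. Its variance is (1 − rho²)/64 + (1 − rho)²/80, which in these units is (1 − rho²) + 0.8(1 − rho)².
- Common baseline mean, or own baseline as covariate: 1 − rho².

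For example, at rho 0.5 the first is 0.75 + 0.8 × 0.25 = 0.95 and the second is 0.75, so the ratio is 0.95/0.75 = 1.27. A generalized least squares calculation gave the same variances.

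Power uses the noncentral t with 126 degrees of freedom and noncentrality 0.5/√(2V/64), where V is the variance in the table.

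| rho | V, free means | V, adjusted | Excess variance | Power, free | Power, adjusted |
|---|---|---|---|---|---|
| 0.3 | 1.302 | 0.910 | 43% | 69% | 84% |
| 0.5 | 0.950 | 0.750 | 27% | 82% | 90% |
| 0.7 | 0.582 | 0.510 | 14% | 96% | 98% |
| 0.9 | 0.198 | 0.190 | 4% | about 100% | about 100% |

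The normal approximation moves the power figures by less than one point (at rho 0.3, 70% against 84%; at rho 0.5, 83% against 90%).

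**When the interaction does worse than ignoring baseline.** Setting (1 − rho²) + 0.8(1 − rho)² = 1 gives rho² + 8·rho − 4 = 0, so rho = −4 + √20 = 0.47. Below that value, the free-means contrast is less precise than a plain comparison of 15-month values.

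**Which outcomes.** The calculation treats baseline balance as due to chance. It therefore applies most directly to outcomes that are not minimization factors: A1c, lipids, blood pressure, CRP, SF-12 and PHQ-9. BMI, fasting glucose and waist circumference are minimization factors.

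**The case against.** The strongest reply is that the inefficient model is inferred. The article never says that each arm has a free baseline mean, and a mixed model with a common baseline mean also tests time-by-group interactions. The Sample Size section shows that some baseline adjustment is expected, and covariate lists are often left to an analysis plan, which is not shown here. This stands as a limit on the claim: the article leaves the point open and does not rule adjustment out. It does not remove the point. The article does fix the test and carries it to every secondary outcome, and that test in its usual form is the less precise one.

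Four stronger readings are tempting and are not supported:

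- *That treating baseline as a response costs precision.* It does not. With a common baseline mean, baseline stays a response and nothing is lost. The loss comes from separate baseline means.
- *That the 80% power depends on an adjustment the analysis does not make.* The article says the calculation leaves the adjustment out, and 80% reproduces without it. For BMI, with rho assumed near 0.9, the two forms differ by about 4% in variance.
- *That chance baseline imbalance adds bias through regression to the mean.* Over repeated randomizations the contrast is unbiased and the test valid. Imbalance is part of the variance already counted above.
- *That the loss is that of a pure change score*, with variance 2(1 − rho) and an excess of 54% at rho 0.3 or 33% at rho 0.5. Those figures assume complete data. With the planned 20% loss, the likelihood also uses the baselines of the 16 per arm without a 15-month value, and the excess falls to 43% and 27%.

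**Conclusion.** The point holds as one of efficiency and clarity. The plan fixes a time-by-group test for the secondary outcomes without stating a common baseline mean or own-baseline adjustment, and its two statistical sections do not make clear what baseline adjustment is intended.

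If the usual unconstrained form is fitted, the loss is material for outcomes with rho around 0.5 or lower and minor from about 0.7 upward. No secondary outcome can be assigned a rho from the documents, so which outcomes lose, and by how much, remains an assumption. Neither the validity of the tests nor the stated BMI power is in question. The change is worth making because it uses data already scheduled and costs almost nothing.

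**What to change.** Add a sentence to Data Analysis along these lines: for each secondary outcome, and in the same form for BMI, the mixed model constrains the arms to a common baseline mean by dropping the group main effect and keeping time and the time-by-group terms at the follow-up visits. The 15-month difference of each intervention from usual care is then reported.

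An equivalent wording is to model the follow-up visits only, with the outcome's own baseline as a covariate interacted with visit. For CRP this is an ANCOVA of the 15-month value on the baseline value.

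This would bring Data Analysis into line with the baseline adjustment mentioned under Sample Size, where the intended variables should also be named. The cost is one sentence and a changed model statement, with no new data and no additional participants.

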### Recruitment and Screening Process

Target sample size for E-LITE is 240, recruited in three sequential cohorts. The screening process for each cohort begins with identification using relevant data available in the patient's electronic health record of age-appropriate, potentially eligible patients whose primary care provider (PCP) regards the interventions under study to be medically appropriate and safe for that patient. Patients whose participation is approved by their PCP are asked to complete a brief questionnaire regarding major exclusions, either online or by phone. Those who pass the initial screen are scheduled for a formal eligibility determination (baseline) visit (BV1), and, within two weeks prior to the visit, they are contacted and given instructions for completion of an online baseline questionnaire.

The BV1 occurs no more than four months after the initial screen and no more than four weeks prior to randomization. It includes completion of additional eligibility questionnaires, measurement of height, weight, waist circumference, and resting blood pressure, and a fasting blood draw for tests of plasma glucose and lipids at the onsite Clinical Laboratory. Time permitting, a seven-day physical activity recall [24] is completed; otherwise, it will be completed at the baseline assessment/randomization visit (BV2). Participants are given instructions and a three-day food record form to be completed and returned at BV2. Participants who have possible angina or peripheral vascular disease based on the Rose Questionnaire [25] are referred to their PCP for further evaluation and may only continue with explicit authorization of their physician.

Participants who are eligible to continue on the basis of BV1 are scheduled for BV2, which occurs at least seven days after BV1 and no more than three weeks prior to the start of the intervention. The BV2 includes measurement of weight, waist circumference, and resting blood pressure, a review of the three-day food record for completeness, complete review of medication and supplement use, a non-fasting blood draw for tests of A1c and CRP, and if necessary, completion of the physical activity recall. Following the measurements, participants are randomized.

All participants are properly and adequately informed and give appropriate consent at each step in the screening process of the trial and prior to participating in the post-randomization phase.

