### Randomization and Blinding

Participants are randomized on a 1:1:1 basis to one of three arms: UC, SM, or CM. Pocock's "minimization" procedure [26] is used to assure better than chance group balance with respect to participant age, gender, race, BMI, fasting blood glucose, waist circumference, and use of PAMFOnline, which is PAMF's online patient portal to access his or her own health record (user vs. non-user). For each participant about to be randomized, a computerized randomization algorithm automatically calculates an imbalance score for each of the balancing factors, as the excess or deficit of previously randomized participants in each arm matching the current patient on that factor. These scores are summed over factors to form a total imbalance score, S, for each treatment arm. The randomization probability of assigning the patient to the treatment associated with the smallest S is set to 2/3, and the other two treatments are each assigned a probability of 1/6 based on Efron's biased coin method [27].

A designated research staff member who is not involved in follow-up data collection or data analysis assigns each study arm a non-revealing label, e.g., A, B, or C, and performs actual randomization of the participants. These labels are used in all study documents and other materials to ensure blinding of the investigators and staff responsible for follow-up data collection and analysis to participant treatment assignments throughout the trial.

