CM condition. Participants in the CM intervention receive the GLB program in 12 weekly group sessions led by a study dietitian and exercise physiologist. Both interventionists have training and experience in weight management counseling, and the dietitian has completed the GLB 2-day training workshop offered by the University of Pittsburgh's Diabetes Prevention Support Center. The sessions are conducted in a highly interactive fashion. The GLB Manual of Operations is closely followed, except for the addition of a food tasting activity as part of the check-in process and a 30-minute physical activity demonstration at the end of each session. The food tasting activities are aimed at increasing participant experience with healthy food choices, encouraging them to try new foods that they might not normally try on their own, and stimulating a social, fun and engaging environment. The physical activity demonstrations are aimed at increasing participant awareness of physical activity intensity, experiencing various moderate-intensity activities that are safe and that they can easily incorporate into their daily lives, and increasing participant confidence. E-LITE participants in both CM and SM arms receive a pedometer in the initial session (the group orientation for the SM arm), as opposed to in session 10 as in the original GLB program [13].

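### The named clustering terms omit the session groups in which CM is delivered, so the CM standard errors are too small if outcomes correlate within those groups

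*Protocol article*

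**What the plan says.** **Delivery (Intensive Treatment Phase).** "Participants in the CM intervention receive the GLB program in 12 weekly group sessions led by a study dietitian and exercise physiologist". The same section describes these sessions as strongly interactive, and the Discussion calls the groups small. SM participants attend one group orientation and then follow the programme at home on DVD. No study group sessions are described for usual care.

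**Analysis (Data Analysis).** The model "accounts for the nature of repeated measurements, the blocked design by cohorts, and the clustering of patients within physicians". CM session group is not in that list.

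**Power (Sample Size).** The target is a "net difference of 1/2 of a standard deviation (equivalent to a medium effect size of 0.5) in BMI at 15 months", tested "at a 2-sided α level of 0.05, assuming up to a 20% rate of loss to follow-up", with about 80% power from a t-test. The section adds: "Note that the t-test calculation is conservative because it does not account for variance reduction due to adjustment for baseline variables". The only other reason it gives is the better-than-chance balance between arms. Both reasons reduce variance; nothing that could increase variance is mentioned.

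**The concern.** Delivering one arm in groups makes the design partially nested: CM outcomes may share a group component that the other arms do not have. The document considers clustering and names its sources, but leaves out the one that the intervention itself creates.

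The named terms do not stand in for it. A cohort main effect shifts all arms alike and cannot absorb a component that exists only in CM. Physicians are not stated to be tied to session groups. A random cohort-by-arm term would work only with a single CM group per cohort, and no such term is described.

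CM vs usual care is one of two primary contrasts, each tested at the full 0.05, so nothing absorbs any inflation. The same model serves the secondary outcomes. The possible result is an interval that is too narrow for the more resource-intensive intervention, and a power statement for CM that counts gains but not this loss.

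**Working it through.** **Inputs from the document.** Sample size and cohorts: "Target sample size for E-LITE is 240, recruited in three sequential cohorts". Allocation: "Participants are randomized on a 1:1:1 basis to one of three arms: UC, SM, or CM". Effect 0.5 SD, two-sided 0.05, 20% loss (Sample Size).

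**Reproducing the stated power.** 240/3 = 80 per arm; 80 × 0.8 = 64 evaluable. With independent observations, SE = √(2/64) = 0.177 SD and 0.5/0.177 = 2.828. Normal power = Φ(2.828 − 1.96) = 80.7%; the exact t-test with 126 df gives 80.1%. The stated 80% is arithmetically right, under independence.

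**Assumptions not in the document.** Number of CM groups k = 3, 6 or 9, of equal size; within-group ICC = 0.01, 0.02, 0.05 or 0.10; no clustering in usual care; equal total variance in both arms.

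**Formulas.**
- Evaluable group size: m = 64/k.
- CM design effect: DE = 1 + (m − 1) × ICC.
- Variance ratio for CM vs usual care: R = (1 + DE)/2 = 1 + (m − 1) × ICC/2.
- Type I error of the planned test, which ignores groups: 2 × [1 − Φ(1.96/√R)].
- Power with a corrected SE and normal critical value: Φ(2.828/√R − 1.96).
- Power with a corrected SE and Satterthwaite df: noncentral t, df = (v_C + v_U)² / [v_C²/(k − 1) + v_U²/63], where v_C = DE/64 and v_U = 1/64.

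**Example, k = 6, ICC 0.05.** m = 10.67; DE = 1 + 9.67 × 0.05 = 1.483; R = 1.242; √R = 1.114. Type I error = 2 × [1 − Φ(1.759)] = 7.9%. Corrected power = Φ(2.538 − 1.96) = 72%; with 13.5 df, 65%.

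| Groups | ICC | R | Type I error, planned test | Power, corrected SE (normal) | Power, corrected SE (Satterthwaite) |
|---|---|---|---|---|---|
| 9 | 0.01 | 1.031 | 5.4% | 80% | 77% |
| 9 | 0.02 | 1.061 | 5.7% | 78% | 75% |
| 9 | 0.05 | 1.153 | 6.8% | 75% | 71% |
| 9 | 0.10 | 1.306 | 8.6% | 70% | 65% |
| 6 | 0.01 | 1.048 | 5.6% | 79% | 74% |
| 6 | 0.02 | 1.097 | 6.1% | 77% | 72% |
| 6 | 0.05 | 1.242 | 7.9% | 72% | 65% |
| 6 | 0.10 | 1.483 | 10.8% | 64% | 56% |
| 3 | 0.01 | 1.102 | 6.2% | 77% | 63% |
| 3 | 0.02 | 1.203 | 7.4% | 73% | 57% |
| 3 | 0.05 | 1.508 | 11.1% | 63% | 44% |
| 3 | 0.10 | 2.017 | 16.8% | 51% | 31% |

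The type I column and the power columns describe different tests. The planned test, left uncorrected, rejects more often in both situations: at ICC 0.05 its power, Φ((2.828 − 1.96)/√R), is 79%, 78% and 76% for 9, 6 and 3 groups, obtained at the inflated error rates shown.

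**Does a cohort term help?** A simulation at a single time point (20,000 trials per setting, cohort fixed effects in the model) gave type I error of 6.8%, 7.5% and 10.8% for 9, 6 and 3 groups at ICC 0.05, and 4.8-4.9% at ICC 0. The cohort effect does not remove the problem.

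**Could baseline adjustment offset the power loss?** The R-squared needed is 1 − 1/R. At ICC 0.05 this is 0.13 with 9 groups, 0.20 with 6 and 0.34 with 3, taking the ICC to be that of the adjusted outcome.

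**The case against.** **The effect may be small.** Group sessions end at month 3, and the primary endpoint is 12 months later. The Maintenance Phase uses individual secure messaging and describes no further group contact. The text suggests that one dietitian and one exercise physiologist lead all groups, and Treatment Fidelity provides for checklists and audits. This stands: the ICC at 15 months could be low, and at zero there is no inflation. It does not show that the ICC is zero. Potential Mediators names social support as one of two main hypothesised mediators, and Treatment Fidelity itself anticipates drift across treatment waves.

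**The worst case fits the text poorly.** One group per cohort means 80/3, about 27 randomised participants per group, which is hard to call small. This stands; the rows for three groups are an outer bound.

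**The power claim may still be right.** A baseline R-squared of about 0.13 to 0.20 would restore the power at 9 or 6 groups and ICC 0.05. This stands for power. It does not cure the type I error, because a group effect that arises after randomisation remains after baseline adjustment.

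**This is a condensed article.** Random-effect structure and df method are commonly left to the analysis plan. That mitigates the point, but the article does list the sources of clustering, and the list is incomplete.

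A reader might infer that the CM test certainly exceeds 5%, or that the conservative label is false. The document supports neither: it gives no ICC and no number of groups, and the gain from baseline adjustment is not quantified.

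**Conclusion.** The omission is real: CM is group-delivered, and no clustering term named in the article represents its session groups. The consequence is conditional. With any positive within-group correlation, the standard errors for CM vs usual care and CM vs SM are too small; SM vs usual care is essentially untouched.

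Over the more plausible part of the grid (6 to 9 groups, ICC 0.01 to 0.05), type I error is between 5.4% and 7.9%. It reaches about 11% only with three groups at ICC 0.05. The loss of power once the standard error is corrected ranges from negligible to material over the same part of the grid. The stated 80% is not an arithmetic error, and for CM the word conservative is unsupported rather than shown to be wrong.

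This should be fixed, but it does not undermine the design. Confidence in the omission is high; confidence in its size is moderate, because ICC and group number are assumptions.

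**What to change.** 1. Record each CM participant's session group. Attendance at group sessions is already documented (Potential Mediators), so this is one added variable, best captured while groups are running.
2. Add a random session-group effect to the PROC MIXED model that applies to CM only and is zero for SM and usual care, with Satterthwaite or Kenward-Roger degrees of freedom.
3. In Sample Size, say for the CM contrast that the t-test ignores clustering within CM groups and that this may offset the gain from baseline adjustment. Give the planned number of groups and a power range over assumed ICCs.

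**Cost.** Data collection and programming are minor. The statistical cost is a wider CM interval and fewer degrees of freedom. With 6 to 9 groups at ICC 0.05, the df correction takes power from 72-75% to 65-71%. With very few groups it is substantial (63% to 44% at three), and the variance component would itself be poorly estimated, so the number of groups should be settled before the model is fixed.
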